#### Process evaluation

In support of the process evaluation, data regarding the nature and subjective experience of use of the tablet, the FindMyApps app and any other apps used will be collected. All participants will self-report use via a monthly questionnaire, filled in by the researchers in a telephone interview with the caregiver. Data regarding views of and interactions with the FindMyApps app by participants in the experimental group will also be recorded digitally during the intervention period by analytics software. Recorded data with respect to the FindMyApps app will include: app start events, page views, button clicks, media viewing events, and duration of sessions using FindMyApps. Due to restrictions imposed by the Android and iOS operating systems to protect privacy of tablet users, it is not feasible in this study to collect analytics data pertaining to the use of other apps on the tablet.

A purposively selected sample of 30 dyads will participate in more detailed SSIs at the conclusion of the intervention period. The SSI is based on the MRC Framework for process evaluation [30]. These interviews aim to collect information on contextual, implementation and mechanisms of impact factors that may influence intervention outcomes. Contextual factors relate to the background characteristics of participants themselves as well as their social, financial and physical environments. Implementation factors concern how the intervention is introduced and delivered to study participants by the researchers and each other. Mechanisms of impact are the participant responses to and interactions with the interventions which mediate outcomes. The interviews will be conducted by trained interviewers via videocall, using the software Microsoft Teams. A second researcher (observer) will join the videocall to register answers to the open SSI questions and any other comments of participants. Part of the interview will be administered to the person with dementia and part to the caregiver.

### Data management and analysis

Quantitative demographic data and data pertaining to participants who withdrew from the study after randomization (dropouts) will be analyzed with descriptive statistics. Differences between the trial arms will be tested with appropriate (non) parametric differences tests (Chi2, Mann-Whitney U, Student’s t-test).

For the effect evaluation, differences between the groups on the primary outcome measures will be tested by MANCOVA on post-test data, including baseline data and potential confounders as covariates in the analysis. Diagnosis (MCI or dementia) will be included as a fixed factor. We will carry out both intention-to-treat and ‘per protocol’ analyses following completion of data collection. Where we encounter missing data as a result of participants withdrawing from the study, we will use appropriate methods to impute that data and perform sensitivity analyses accordingly. Analyses will be conducted using SPSS. We will primarily report effect sizes with calculated 95% confidence intervals, however we will also report *p*-values. We will use 2-tailed p-values with an alpha of 0.05.

Both a cost-effectiveness analysis (CEA) and a cost-utility analysis (CUA) will be performed from a societal and healthcare perspective according to Dutch guidelines [62] with a time horizon of 3 months. The aim of the economic evaluation is to relate the incremental costs of FindMyApps in comparison with usual care to the incremental clinical outcomes. The following effect measures will be included in the economic evaluation: MSPP and ASCOT (person with dementia); SSCQ (caregiver); and EQ-5D-5L (person with dementia and caregiver). Missing cost and effect data will be imputed using multiple imputation according to the MICE algorithm [63]. Rubin’s rules will be used to pool the results from the different multiply imputed datasets. Bivariate regression analyses will be used to estimate cost and effect differences between FindMyApps and usual care/tablet use while adjusting for confounders if necessary. Incremental cost-effectiveness ratios (ICERs) will be calculated by dividing the difference in the mean total costs between the intervention groups by the difference in mean effect between the intervention groups. Cost-effectiveness acceptability curves will also be estimated showing the probability that FindMyApps is cost-effective in comparison with usual care/tablet use for a range of different ceiling ratios thereby showing decision uncertainty [64].

Trained researchers will provide verbal and written information to all potential participants to inform them about the nature of the study and the inherent benefits and risks. Participants will be advised to consider the information discussed before being invited to provide written, informed consent to participate. Informed consent forms will be sent to participants by post. If they wish to participate in the study, participants will be requested to return signed informed consent forms by pre-paid post to the research team. Participation in the study is conditional on both members of the dyad providing such written consent and consent will also be an ongoing process: participants will be asked on a regular basis if they are still willing to proceed with the intervention and the study [65].

All trial data will be entered electronically and stored on a secure server, based in the European Union, via Castor EDC. All data entry screens resemble the original paper versions of the corresponding forms. To help avoid error and allow checks at the time of data entry, radio buttons are employed throughout, instead of drop-down menus. Where applicable, data validation checks are applied automatically. Access to the database is password protected and the activities that each user can undertake are limited by individual access rights.

The executive researcher will be responsible for monitoring study progress, reporting on missing data and taking necessary action to follow-up on missing data or discrepancies.

With respect to the processing of personal data, a data privacy impact assessment has been carried out for this study and will be reviewed on a regular basis. Personal data will be processed in line with relevant legislation including the General Data Protection Regulation.

All data will be stored securely. Original participant files and the key to the code linking personal details and coded study data will be stored securely in a locked cupboard to which only the FindMyApps researchers have access, in a locked office, in a secure building. Original files will be stored in numerical order and maintained for a period of fifteen years after completion of the study. Any personal data stored electronically will be kept on a secure server, in a password-protected environment to which only the researchers directly involved in administering and supervising the study have access.

Data-monitoring will be undertaken by members of the project commission, with specialist input from professional statisticians as required. Given the low risk of harm posed by FindMyApps as a non-clinical intervention, and the relatively small size of the study, an independent data-monitoring committee is not necessary or valuable. There is no interim statistical analysis planned. All study investigators will have access to full data-sets.

Audits will be conducted by research and quality assurance personnel who are independent of the study, according to the established procedures of the Amsterdam Public Health Research Institute. Audits will take place once the set-up of the trial is complete and before recruitment starts (approximately month 4); at the midpoint of the study period (approximately month 18); and after recruitment is completed, during analysis of the data (approximately month 30). Any changes to the protocol that may impact upon study participants will be submitted to the medical ethics committee of VUmc and the scientific quality committee of APH for review.

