### Sample size

Two pilot randomized controlled trials preceded this definitive trial, both of comparable design with comparable outcome measures [36, 37]. Values of partial eta squared with respect to primary outcomes measured with instruments which will also be used in the present study, were found to range from 0.01 (MSPP) to 0.38 (PAL). These correspond to small to large effect sizes, respectively, when compared to Cohen’s suggested benchmarks [38]. Previous evaluations of interventions implemented in the Netherlands to improve social health in dementia have also found moderate to large effect sizes, with respect to similar outcome measures [39, 40]. Whilst both pilot studies also revealed small between group differences with respect to a number of outcomes, this trial will not be powered to detect small effects of the intervention. We do not believe that small effects of the intervention – even if statistically significant – would be ‘clinically’ significant. We therefore do not feel that we could justify the additional use of public funds to conduct the trial in such a way as to have adequate power to detect small effects of the intervention.

Effects of the intervention on primary outcomes for the primary participants (social participation and self-management) will be tested using MANCOVA. An a priori power calculation was conducted using the software G*Power, version 3.1, for main effects MANOVA, assuming two dependent variables, two groups, alpha = 0.05 and power = 0.8, and a moderate overall effect. The total required sample size would be *n* = 158. This is an overestimate of the required sample size to achieve a power of 0.8 because the inclusion of covariates in the MANCOVA is expected to increase the statistical power of the test compared to MANOVA (thereby reducing the required sample size for the desired power of 0.8).

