### Allocation

Participants will be randomly assigned to either the FindMyApps (experimental) or usual care (control) arm. Randomization will be performed via Castor EDC, following a variable blocked randomization method, with a target of 1:1 allocation and randomly selected block sizes of 4 or 6. Group allocation will be stratified on the basis of diagnosis (MCI or dementia) and any prior experience with the use of a tablet (participant self-report; ‘Yes’ or ‘No’).

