## Discussion

Two pilot RCTs helped to establish a protocol for the evaluation of the feasibility and effectiveness of the FindMyApps intervention. Although the protocol for the present study was amended in light of the 2020 coronavirus pandemic, this study goes further than any previous study of the FindMyApps intervention in four important ways.

First, by conducting the effect evaluation in a larger study (n_tot_ = 150; 75 experimental group, 75 control group), we hope to conduct this trial with a reasonable power to detect medium effect sizes (MANCOVA: η^2^ = 0.06; power 0.80, alpha = 0.05), to be able to conduct analyses from which robust conclusions about the intervention’s effectiveness for the target group of community dwelling people living with MCI/dementia and their caregiver can be drawn. A frequent criticism of eHealth or digital health interventions has been a lack of scrutiny in the context of high quality RCTs [11]. This trial will also contribute to the growing pool of RCTs in the field of eHealth and digital health, which is needed for the field to mature.

Second, by means of a process evaluation to review implementation of the FindMyApps intervention among a larger group of participants, we aim to leverage better insight into the contextual, implementation and mechanisms of impact factors that may influence implementation and adoption of FindMyApps, and the study outcomes. This will better inform further evaluation and implementation of FindMyApps compared with existing research.

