Third, we aim to extend recruitment for the study from a regional to a national level, to include participants from throughout the Netherlands. With the exception of the three characteristics on which participants are stratified prior to group allocation (diagnosis of MCI or dementia; whether the participant has previously used a tablet or not; and whether or not the caregiver cohabits with the person with dementia), there is no a priori hypothesis regarding subgroups who may derive more benefit from FindMyApps. The trial is therefore designed to be as representative and ecologically valid as is feasible within the scope of a controlled trial. By recruiting people with dementia of different etiologies and with a broad demographic base, the conclusions drawn from this trial will be applicable to a broad group of people with dementia and at a national level. This is important for the planning of large-scale implementation of the FindMyApps intervention if it proves to be effective. Regardless of the main effect and cost-effectiveness analyses, subgroup analyses in the present study may suggest hypotheses relating to effectiveness or cost-effectiveness for specific target groups, which could form the basis of future studies.

Fourth, this trial incorporates for the first time a cost-effectiveness analysis. If a main effect of the FindMyApps intervention is found, we will also be able to conduct an analysis allowing a comparison of the cost-effectiveness of FindMyApps with other interventions targeting similar outcomes in similar target groups and settings. Combined with the effect analyses, this will directly inform decision-making by policy-makers, care funders, care providers and individuals with respect to the implementation of the FindMyApps intervention, and/or other interventions which target similar outcomes. As such, the present study will support the efficient use of limited resources within the care sector in the Netherlands to improve the lives of community-dwelling people with dementia and their caregivers.

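### Allocation lists two stratification factors and the Discussion three, and the primary MANCOVA names only one of them, diagnosis

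*Protocol article*

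**What the plan says.** Three places in the protocol article bear on this.

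- **Allocation:** "Group allocation will be stratified on the basis of diagnosis (MCI or dementia) and any prior experience with the use of a tablet", the latter self-reported as yes or no. Blocks are of varying size, "with a target of 1:1 allocation and randomly selected block sizes of 4 or 6".
- **Discussion**, third of the four listed advances: "With the exception of the three characteristics on which participants are stratified prior to group allocation". The list that follows repeats diagnosis and previous tablet use and adds "whether or not the caregiver cohabits with the person with dementia". The sentence exempts these three from its statement that there is no prior hypothesis about subgroups.
- **Data management and analysis:** the primary outcomes are tested by MANCOVA on post-test data, "including baseline data and potential confounders as covariates in the analysis". The next sentence is "Diagnosis (MCI or dementia) will be included as a fixed factor". Neither tablet experience nor cohabitation is mentioned.

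Cohabitation otherwise appears only under Eligibility criteria, as one way for a caregiver to meet the contact requirement.

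**The concern.** The analysis should reflect how participants were randomised. Stratified blocks balance the arms on each stratifier, so the treatment estimate varies less from trial to trial than it would under simple randomisation. A model without the stratifier still counts that factor's variance as residual error. Its standard error is then too large and its test conservative. Naming one of the two Allocation stratifiers leaves the other to a covariate list that this article does not fix.

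The conflict over the factors comes first. A reader cannot tell from the article which factors the model should carry. Cohabitation is also presented as a stratifier with prior subgroup standing, although Allocation does not use it.

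Power makes this worth settling. The Sample size section relies on covariates to do better than its MANOVA calculation, and the first randomisation target (75 per group, 150 in total) is already below the 158 calculated.

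**Working it through.** **1. The factor lists side by side**

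| Section | Factors | Strata |
|---|---|---|
| Allocation | diagnosis, tablet experience | 2 × 2 = 4 |
| Discussion | the same two plus cohabitation | 2 × 2 × 2 = 8 |
| Primary model | diagnosis is the only stratifier named | n/a |

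**2. The plan's own sample size.** The stated inputs are "assuming two dependent variables, two groups, alpha = 0.05 and power = 0.8, and a moderate overall effect". For a two-group MANOVA with two outcomes, power is P(F > critical value), with df1 = 2, df2 = N − 3 and noncentrality f²·N. Taking moderate as f² = 0.0625 (an assumption), N = 158 has power 0.802, so the stated 158 reproduces. The Discussion gives "MANCOVA: η^2^ = 0.06; power 0.80, alpha = 0.05"; converting that to f² = 0.06/0.94 gives N = 154. With f² = 0.0625, power is 0.780 at N = 150 and 0.676 at N = 120, which is 150 less 20% dropout.

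**3. Cost of adding factors that predict nothing.** Each binary factor takes one from df2. At N = 150, power goes from 0.7796 to 0.7795 with one or two factors. At N = 120 it goes from 0.6757 to 0.6756 (one) or 0.6755 (two).

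**4. Cost of omitting a prognostic factor, one outcome.** Let the factor explain a share R of the variance and be exactly balanced across arms. Omitting it shrinks the t statistic by √(1 − R).
- Type I error is P(|t| > 1.980/√(1 − R)) on 118 df at n = 120. For R = 0.05 it is 0.044. For R = 0.10 the cut-off is 1.980/0.9487 = 2.087 and the result is 0.039.
- For d = 0.5 the noncentrality is 0.5·√120/2/√(1 − R). Power without and with the factor is 0.78 and 0.80 at R = 0.05, and 0.79 and 0.82 at R = 0.10. The loss is about 2 to 3 points.

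**5. Two outcomes, as planned.** This is a simulated MANCOVA with blocks of 4 or 6 in four strata, N = 150 and 4,000 trials per setting. Outcomes are read as what remains after baseline adjustment. The factor explains the same share of each.

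| Share | Type I, omitted | Type I, included | Power, omitted | Power, included |
|---|---|---|---|---|
| 0% | 0.051 | 0.050 | 0.778 | 0.784 |
| 5% | 0.047 | 0.046 | 0.761 | 0.796 |
| 10% | 0.037 | 0.056 | 0.758 | 0.806 |

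The Monte Carlo standard error is about 0.003 for type I error. The power loss is about 3.5 points at 5% and 4.8 points at 10%. Each model was run on separate data, so each gap has a standard error of about 0.9 point: √(0.758·0.242/4000 + 0.806·0.194/4000) = 0.009.

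I repeated this with both models fitted to the same data, 6,000 trials per setting. At N = 150 the gap was nil at 0%, 3.3 points at 5% (0.771 against 0.804) and 7.2 points at 10% (0.745 against 0.817). At N = 120 the 10% gap was 8.4 points (0.630 against 0.714). This set-up is unfavourable: the outcomes are otherwise uncorrelated, and the factor moves both in the same direction as treatment. In a balanced design of 152 with treatment effects in opposite directions on the two outcomes, the 10% loss was about 1 point (0.780 against 0.790).

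**6. What baseline adjustment leaves.** Suppose the factor explains a share R of both the baseline and the post-test variance, with within-stratum correlation ρ. Its share of what remains after baseline is R(1 − ρ)/[1 + ρ + R(1 − ρ)].
- R = 0.05: 0.025/1.525 = 1.6% at ρ = 0.5, and 0.015/1.715 = 0.9% at ρ = 0.7.
- R = 0.10: 0.05/1.55 = 3.2% at ρ = 0.5, and 0.03/1.73 = 1.7% at ρ = 0.7.

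Put into step 4, these shares give type I error of about 0.046 to 0.049. Power without and with the factor is 0.776 and 0.779 at 0.9%, and 0.779 and 0.788 at 3.2%, a loss of under 1 point.

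**The case against.** The strongest reply is that tablet experience is unnamed rather than excluded. It is a baseline variable, the wording on confounders leaves room for it, and a journal article commonly leaves the covariate list to an analysis plan. This stands in part: the article does not say the factor will be left out. But it is not silent on stratifiers either. It names one as a model term and not the other.

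A second reply is that Castor holds the factors actually used, so the sponsor can always align the analysis. That is right, and the conflict is one of documentation. It still needs correcting.

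A reader might infer more than the article supports:

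- **That a false positive or a biased estimate is at risk.** The error runs the other way: the test becomes conservative.
- **That the planned tests of arm differences will choose the covariates.** Those tests are described with the demographic and dropout data. No sentence links them to the model.
- **That tablet experience is the most prognostic factor.** Nothing in the article shows this. The participant outcomes are self-management and social participation, and both arms receive a tablet and basic instruction. Experience might modify the intervention's effect, but only prediction of the outcome drives the loss computed here.
- **That cohabitation's subgroup standing is invalid.** A subgroup analysis does not need stratification, and the Discussion treats such analyses as a source of hypotheses.

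**Conclusion.** The contradiction between Allocation and Discussion is certain and rests on no assumption. The model point is moderate: one stratifier given in Allocation is not fixed as a term in the primary analysis.

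If that factor is left out, and if it explains 0 to 10% of the variance remaining after baseline adjustment, type I error is about 0.05 down to 0.04. The power loss is 0 to about 3 to 5 points. That figure is not a strict bound: in the least favourable arrangement checked, the loss at 10% was 7 to 8 points. The lower end is more likely once baseline values are in the model, because a factor that acts equally on baseline and follow-up then has little left to explain. The 0 to 10% range and the correlations of 0.5 to 0.7 are assumptions; the article gives neither.

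**What to change.** 1. Make Allocation and Discussion list the same stratification factors, namely those configured in Castor. If cohabitation was not one of them, remove it from the Discussion's list of stratifiers and, if it is still of interest, describe it there only as a subgroup characteristic. If it was one, add it to Allocation.
2. In Data management and analysis, state that the primary model contains arm, baseline values of the outcomes and every stratification factor actually used, as prespecified terms.

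This takes a sentence in each place and about one error degree of freedom per factor, under 0.1 point of power if the factor predicts nothing. A factor used to stratify is already recorded at randomisation, so no new data are needed. The stated total of 158 does not change.

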### Ancillary and post-trial care

All participants, regardless of the trial arm to which they are allocated, will be offered ongoing access to the FindMyApps selection tool after the three-month study period. Study participants who have used a tablet loaned from the research organization and who wish to subsequently purchase a tablet be offered advice about the most cost-effective ways for them to obtain a tablet for themselves.

### Dissemination policy

The results of the main effect, cost-effectiveness and process analyses will be submitted as separate articles for publication in academic, peer-reviewed journals. It is anticipated that the main trial results will be submitted for publication within 6 months of completion of data collection. The results of this trial are therefore expected to be published in 2023. Study participants will be offered the opportunity to receive a summary of the main trial results. We also anticipate sharing the results with health professionals and other researchers through presentations at relevant national and international conferences. Results of the trial, including interim reports, will also be collected as part of the routine reporting of the EU Marie Sklodowska-Curie Innovative Training Network DISTINCT, through which this trial is funded. Anonymized data collected with the TOPICS-MDS instrument will be shared with the TOPICS national database, following completion of the study.

